### Participant timeline

The time schedule of enrolment, interventions, assessments and visits for participants is shown in Table 1.

**Table 1 Tab1:** Participant timeline of the visits and assessments

VISITS	Pre-Treatment (Screening, Waiting time, Baseline/Visit 1 Randomisation)				Treatment					Post-Treatment Follow-up	
						Phone Visit 2–3	Visit 4	Phone Visit 5–6	Visit 7	Phone Visit 8–12	Last Visit, EOT
**TIME**			**Week − 4 to Day − 1**		**Day 0**	**Month 1 & 2**	**Month 3**	**Month 4 & 5**	**Month 6**	**Month 7–11**	**Month 12**
**Pre-Screening**	**X**										
**Waiting time**		**X**									
**Randomisation**				**X**							
**Informed consent**			**X**								
**In-, exclusion criteria**			**X**								
**Demographic Data**			**X**								
**Handing out Study Book**					**X**						
**Fall prevention information**					**X**						
**Recommendation to visit primary care doctor**					**X**						
**Start treatment or control per participant**					**X**						
**Review fall diary**						**X**	**X**	**X**	**X**	**X**	**X**
**BBS**			**X**				**X**		**X**		**X**
**MoCA**			**X**				**X**		**X**		**X**
**IADL**			**X**				**X**		**X**		**X**
**Medications**			**X**				**X**		**X**		**X**
**Baseline Questions**			**X**								
**Short FES-I**			**X**				**X**		**X**		**X**
**GDS-15**			**X**				**X**		**X**		**X**
**SF-12**			**X**				**X**		**X**		**X**
**ICPH (only EYT and Tai Chi group)**							**X**		**X**		
**FIMA**			**X**				**X**		**X**		**X**
**Safety; complications**						**X**	**X**	**X**	**X**	**X**	**X**
**Adherence, motivation, additional interventions**									**X**		

### Sample size

Sample size calculation is based on the assumptions on the proportion of participants with at least one fall during a six-month period. The proportion of participants with at least one fall is assumed as 50% in the standard care group [44, 53]. A decrease of this proportion to 35% is considered clinically relevant and achievable by EYT and Tai Chi [54]. The study is planned with 80% power to show the difference between treatments at the two-sided level alpha of 5% when the proportions of fallers (i.e. participants experiencing at least one fall within 6 months) is 50% with standard care and 35% with both EYT and Tai Chi. According to the chi-square distribution, 155 participants per group (calculated with NQuery Advisor 7.0) are required. The sample size calculation is performed for the three-group comparison. To account for multiplicity issues in this three-group comparison, a closed test procedure at the two-sided level alpha of 5% will be used. That is, the global null hypothesis of no differences between any of the three intervention types will be tested first, and if it can be rejected, pairwise group comparisons will be conducted each at the two-sided level alpha of 5%. The two-group comparison of EYT versus standard care has a power of 80% when the proportion of fallers is reduced from 50 to 34.3%. The two-group comparison of EYT versus Tai Chi has a power of 80% when the difference in the proportion of fallers is 15%. To account for a certain amount of non-compliance and incomplete observations, 550 participants will be randomised at a ratio of 1:1:1.

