### Statistical analysis

The primary efficacy analysis will be performed according to the intention-to-treat principle. All randomised participants will be analysed as belonging to their randomised arm, regardless of whether they refused therapy or whether other protocol deviations are known.

For the analysis of the primary endpoint fall (yes, no) within 6 months, a time-to-event methodology will be applied using the time to the first fall to account for the potentially incomplete observation times of the participants. This is considered to be more efficient than an analysis of the binary endpoint fall (yes, no), therefore leading to a gain in power. For participants who do not fall within the six-month observation period, the time to last contact will be used as censored observation. Death without a previous fall will be regarded as a competing event in the analysis. A Cox regression model will be used to test the efficacy of EYT versus Tai Chi versus standard care in reducing the risk of falling within 6 months after handing out the study book. The model will include the intervention type, trial site, BBS score and age as the independent variables. To account for multiplicity issues in this three-group comparison, a closed test procedure at the two-sided level alpha of 5% will be used. That is, the global null hypothesis of no differences between any of the three intervention types will be tested first, and if it can be rejected, pairwise group comparisons will be conducted each at the two-sided level alpha of 5%. Hazard ratios between the interventions will be calculated from the model with a two-sided 95% CI. In addition to the overall comparison of the treatment arms, a comparison of treatments in the key participant subgroups will be of interest. The treatment effect will be estimated separately in the participants defined by different diagnoses (present vs. absent) from the regression models, including the interaction between treatment and diagnosis.

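### The 80% power stated for EYT versus standard care at 34.3% is that of an ungated two-group test; through the planned closed test it is about 75–76% if Tai Chi performs similarly, and 71% at 50/35/35

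*Protocol article*

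**What the plan says.** All statements are in the protocol article.

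- **Basis of the sample size (Sample size).** "The sample size calculation is performed for the three-group comparison". The power target is worded "The study is planned with 80% power to show the difference between treatments at the two-sided level alpha of 5" per cent, when the proportion of fallers "is 50% with standard care and 35% with both EYT and Tai Chi". The result is "155 participants per group (calculated with NQuery Advisor 7.0) are required".
- **Closed test (Sample size, repeated under Statistical analysis for the primary Cox model).** "the global null hypothesis of no differences between any of the three intervention types will be tested first"; then "if it can be rejected, pairwise group comparisons will be conducted each at the two-sided level alpha of 5" per cent.
- **Pairwise power (Sample size, directly after the closed test).** "The two-group comparison of EYT versus standard care has a power of 80% when the proportion of fallers is reduced from 50 to 34.3" per cent. Then: "The two-group comparison of EYT versus Tai Chi has a power of 80% when the difference in the proportion of fallers is 15" per cent. The first sentence gives no Tai Chi rate. The second gives no proportions, only a difference.
- **Number randomised (Sample size).** 550 participants, 1:1:1. The excess over 3 × 155 = 465 is set aside for non-compliance and incomplete observation.
- **Expected pattern.** The same section plans 35% for both active arms, and the Discussion expects EYT and Tai Chi to have similar effects on falls.

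**The concern.** The primary objective is whether EYT and Tai Chi reduce the risk of falling. The global test cannot answer that, because rejecting it does not say which arms differ. The answer comes from the pairwise step, which is reached only after global rejection. The power for EYT versus standard care is therefore the probability that two tests both reject, and this cannot exceed the power of either one alone.

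The pairwise figure follows straight after the two-step procedure, with nothing to say that it leaves the first step out. A reader will take 80% as the chance that the trial shows EYT superior at a 34.3% faller rate. What is at stake is the accuracy of that statement. Type I error, the decision rule and the analysis model are not affected.

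**Working it through.** **Inputs (Sample size section).** n = 155 per arm; two-sided alpha 5%; standard care 50%; active arms 35% (planning alternative) or EYT 34.3% (pairwise sentence). Assumption: the Tai Chi rate that goes with EYT at 34.3% is not given, so a range is shown.

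**1. Global test, reproducing the article's figure.** For three equal groups the noncentrality is n·Σ(pᵢ − p̄)² / [p̄(1 − p̄)], with 2 df.

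- p̄ = (0.50 + 0.35 + 0.35)/3 = 0.40
- Σ(pᵢ − p̄)² = 0.10² + 0.05² + 0.05² = 0.015
- Noncentrality = 155 × 0.015/0.24 = 9.69; critical value 5.991; power 80.2%

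With 154 per group the power is 79.96%, so 155 is the first n above 80%. The sample size is confirmed as that of the global test.

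**2. Stand-alone pairwise test, reproducing the article's figure.** Power = Φ{[d√n − 1.96·√(2p̄(1 − p̄))] / √(p₁(1 − p₁) + p₂(1 − p₂))}.

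- 50% vs 34.3%: (0.157 × 12.45 − 1.96 × 0.698)/0.689 = 0.85; power 80.2%
- 50% vs 35%: (0.150 × 12.45 − 1.96 × 0.699)/0.691 = 0.72; power 76.4%

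So the stated 80% at 34.3% is correct for a two-group test with no global test before it.

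**3. Closed test.** One million simulated binomial trials per scenario, 155 per arm. EYT versus standard care counts as shown only if the three-group chi-square exceeds 5.991 and the pairwise chi-square exceeds 3.841. Standard care is 50% throughout.

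| EYT | Tai Chi | Ungated EYT vs standard care | Closed test |
|---|---|---|---|
| 34.3% | 25% | 80% | 80% |
| 34.3% | 30% | 80% | 79% |
| 34.3% | 34.3% | 80% | 76% |
| 34.3% | 35% | 80% | 75% |
| 34.3% | 42% | 80% | 70% |
| 34.3% | 50% | 80% | 76% |
| 35% | 35% | 76% | 71% |

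The loss is largest when Tai Chi lies about midway between EYT and standard care, because the global test is weakest there. At 50/35/35 the closed-test power is also 71% for Tai Chi versus standard care; it is 63% for showing both active arms superior and 80% for at least one.

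**4. Splitting the 71%.** From 80% to 76% is the move from a 15.7-point to a 15-point difference. From 76% to 71% is the global test.

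**5. EYT versus Tai Chi at 15 points, 155 per arm, standard care 50%.**

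| Active-arm rates | Ungated | Closed test |
|---|---|---|
| 50% and 35% | 76% | 71% |
| 42.5% and 27.5% | 80% (79.5%) | 79% |
| 35% and 20% | 85% | 85% |

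Here the global test costs almost nothing unless one active arm is close to standard care. What moves the figure is where the two proportions lie, and the article does not say.

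**The case against.** **No printed figure is miscalculated.** This stands. The article says that the sample size is for the three-group comparison, and both 80% figures checked in steps 1 and 2 reproduce. The pairwise sentence is literally true of an isolated two-group test and never says in words that it is power through the closed test. But the plan makes no isolated two-group claim, and the sentence follows the two-step rule without a qualifier.

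**The article does not promise 80% pairwise power at 35%.** This also stands. Quoting 34.3% tells a careful reader that pairwise power at 35% is below 80%. One might infer that the whole drop from 80% to 71% comes from overlooking the global test; only about 5 of the 9 points do.

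**The size of the loss depends on a Tai Chi rate that the article does not give.** True. The 70% low needs Tai Chi near 42%, which nothing in the article plans. At the rates the article itself points to, the loss is 4–5 points.

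**The real trial will have more power than 155 per arm on a chi-square basis.** Partly. With all 550 evaluable (about 183 per arm), closed-test power would be 79.7% at 50/35/35 and 84% at 50/34.3/34.3. These are upper limits, since the excess is reserved for non-compliance and incomplete observation. The Statistical analysis section also expects the Cox model to be more efficient, but gives no amount. Neither changes what a figure stated on the chi-square basis at 155 per arm means.

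**EYT versus Tai Chi.** A reader might infer that the 15% sentence suffers in the same way. In general it does not, as step 5 shows; its fault is the missing proportions.

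**Conclusion.** The point holds as a misdescription of power. It is not a calculation error. The 80% at 34.3% leaves out the global test that the plan requires first. At 155 per arm on the chi-square basis, the power of the planned procedure is about 75–76% if Tai Chi is similar to EYT (34.3–35%). It is about 70% at worst among the rates examined (Tai Chi near 42%, an assumption), and there is almost no loss if Tai Chi is 25% or lower. At 50/35/35 it is 71% for each active arm and 63% for both, while the global test keeps its stated 80%.

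A reader might go further and conclude that the sample size of 155 is wrong or that the closed test is invalid. The article supports neither: 155 is right for the test it was computed for, and the procedure itself is not in question. The correction is modest, but it concerns the claims the trial is meant to support.

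**What to change.** Change the Sample size section as follows.

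1. State that 80% with 155 per arm is the power of the global three-group test at 50/35/35.
2. Replace the 34.3% sentence with closed-test power: about 76% for EYT versus standard care at 50/34.3/34.3, and at 50/35/35, 71% for each active arm versus standard care and 63% for both. If the 34.3% figure is kept, label it as the power of a stand-alone two-group test and give the closed-test value beside it.
3. Give the two proportions behind the 15% figure for EYT versus Tai Chi, since the ungated power for 15 points runs from 76% (50% vs 35%) through 80% (42.5% vs 27.5%) to 85% (35% vs 20%).

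The cost is text only. The number randomised, the testing procedure and the analysis stay as they are; the stated pairwise power becomes slightly less favourable.

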### Recruitment

The trial will be announced through local media, a web page (https://www.uniklinik-freiburg.de/entaier-studie.html), flyers, posters and personally to elderly people and to key people in contact with the elderly (senior citizens, physicians, hospitals, pharmacies, ambulances, nursing services, household help, food banks, social workers, social welfare office).

Potential participants contacting the local trial site will be pre-screened through a phone call. Elderly people that appear to be eligible will enter a waiting time until 15 or 30 participants could be enrolled. Only then will they receive detailed information. After providing their written consent, they are screened, enrolled and assessed for the baseline by the local trial sites. Within four subsequent weeks, they are randomly allocated to the three groups and receive their study book containing the dairies and all relevant information. This step initiates the observation period and is immediately followed by the start of the EYT and Tai Chi sessions.

## Methods: assignment of interventions

### Randomisation

Central randomisation by fax will be performed in this trial (CTU). Randomisation will be stratified by clinical site and performed in blocks of length 12, 15 or 18 at a ratio of 1:1:1. The randomisation code will be produced by validated programmes based on the Statistical Analysis System. For each batch size (12, 15 and 18), a separate randomisation fax form and randomisation lists will be prepared.

### Blinding and minimising risk of bias

The blinding of the Tai Chi and EYT group and the standard care group to their allocation is not possible because it is obvious in which group the participants are randomised, as all three trial interventions differ substantially. The outcomes are either directly reported by the participants (falls, questionnaires) or in close communication with the participants (falls, complications, BBS, MoCA, IADL). Therefore, also a reliable blinding of the outcome assessment to participant allocation is not possible. Outcome assessors are instructed by a written guide to start with open and general questions and to avoid mentioning the group allocation as long as possible. Since the electronic case report forms differ depending on randomized treatment, the statistical analysis will not be blinded, but all confirmatory analyses are prespecified in the clinical trial protocol and decisions on analysis data sets will be finalized without access to the unblinded data. Concealment of the randomisation will be guaranteed to minimise selection bias. All assessments will be conducted in a comparable setting and time. The primary outcome parameter is clearly defined and described in detail [42]. The combination of prospective, daily, participant-completed falls diary and monthly calls is regarded to be reliable and captures most of the falls among seniors [55]. To reduce incomplete outcome data, travel costs for public transportation are refunded, and the trial sites may conduct the follow-up visits at the participants’ home. Two of the groups receive interventions in a comparable setting, support and frequency. The third (control) group, although not offered regular training sessions, can still avail of such opportunities through the addresses in the brochure, the general courses in their city or their primary care physician. They receive human attention through an appreciating communication with the trained study personnel and their primary care doctors, other consultants and medical referrals at their discretion and informed by evidence. The patient informed consent (form) makes no remarks on the potential efficacy of EYT or Tai Chi to reduce expectancy bias. Publication bias will be reduced by study registration in the trial registers, the publication of the trial protocol and the results and the support of open data.

## Methods: data collection, management and analysis

### Data collection methods

BBS, MoCA, IADL and the complications are assessed by the study personnel.

The FES-I, GDS-15, SF-12, ICPH and FIMA questionnaires, the falls and training diaries and the self-designed questionnaires (see Supplementary file 1, 2, 3 and 4) are filled in by the participants in the same environment, which is quiet and respectful of the subject’s privacy. As much as possible, the outcome measures are assessed at a consistent time of the day and consistent with the medication cycles, particularly in participants with conditions like Parkinson’s and multiple sclerosis. The data obtained by the investigators are kept in source documents and directly entered in a trial-specific electronic case report form (eCRF). The patient-reported questionnaires are stored as the participants’ source documents, and a duplicate is sent to the CTU in Freiburg to be entered in the eCRF.

### Retention

Participants will be compensated for their travel costs: €110 for the first 6 months and €20 each for the screening and follow-up. If necessary (e.g. social welfare)*,* up to 15% of participants can receive further reimbursement of public transportation costs to visit group classes. Compliance with the trial procedures will be supported through appreciation, expressed gratefulness, giving participants sufficient time to be heard and seen, detailed explanation of the purpose and necessity of such studies to improve elderly care and a small token during every visit of the trial site (e.g. a post card with motifs from art, nature or aphorisms).

Participants may withdraw from the group classes or from the study for any reason at any time. The investigator may withdraw a participant from the intervention if the risks outweigh the benefit or if the inclusion/exclusion criteria are severely violated. Nevertheless, further follow-up visits and the assessment of the trial endpoints will be attempted to conduct an analysis according to the intention-to-treat principle.

Following the recommendation of public and patient representatives (PPR), EYT therapists, Tai Chi teachers and study personnel will receive a 3 h personal and written refresher training in appreciating, encouraging, non-judgmental communication and managing challenges of the group situation provided by a communication trainer. The EYT therapists and Tai Chi teachers will also receive a motivation concept on elderly people to comply with regular exercises, with a specific focus on the elderly living a reclusive life. The motivation concept is based on published research [21, 56, 57–61] and expert consultation.

### Data management, quality control and monitoring

Extensive procedures ensure the quality control of data collection, data entry and subject confidentiality. The study data are collected and managed using REDCap™ Version 8.6.5, a fully web-based remote data entry system based on web forms developed and maintained by the REDCap Consortium ([contact]).

Data entry and data corrections on the e-forms are automatically tracked in an audit trail created by the electronic data capture system. Data will be regularly reviewed for completeness, consistency and plausibility. During the trial, the clinical research associate will visit the trial sites regularly. The clinical research associate will verify if the trial is conducted according to the trial protocol (signed informed consents, eligibility of participants, primary endpoint and safety data), the trial-specific procedures, the International Conference on Harmonisation-Good Clinical Practice guideline (ICH-GCP, R2) and the national/local regulatory requirements and will compare the entries in the eCRF with the source data.

Data will be exported from the database into the statistical software for analysis.

### Statistical analysis

The primary efficacy analysis will be performed according to the intention-to-treat principle. All randomised participants will be analysed as belonging to their randomised arm, regardless of whether they refused therapy or whether other protocol deviations are known.

For the analysis of the primary endpoint fall (yes, no) within 6 months, a time-to-event methodology will be applied using the time to the first fall to account for the potentially incomplete observation times of the participants. This is considered to be more efficient than an analysis of the binary endpoint fall (yes, no), therefore leading to a gain in power. For participants who do not fall within the six-month observation period, the time to last contact will be used as censored observation. Death without a previous fall will be regarded as a competing event in the analysis. A Cox regression model will be used to test the efficacy of EYT versus Tai Chi versus standard care in reducing the risk of falling within 6 months after handing out the study book. The model will include the intervention type, trial site, BBS score and age as the independent variables. To account for multiplicity issues in this three-group comparison, a closed test procedure at the two-sided level alpha of 5% will be used. That is, the global null hypothesis of no differences between any of the three intervention types will be tested first, and if it can be rejected, pairwise group comparisons will be conducted each at the two-sided level alpha of 5%. Hazard ratios between the interventions will be calculated from the model with a two-sided 95% CI. In addition to the overall comparison of the treatment arms, a comparison of treatments in the key participant subgroups will be of interest. The treatment effect will be estimated separately in the participants defined by different diagnoses (present vs. absent) from the regression models, including the interaction between treatment and diagnosis.

For the analysis of the secondary endpoint total number of falls per participant within 6 months after handing out the study book, a negative binomial regression model will be used to test the efficacy of EYT versus Tai Chi versus standard care. A negative binomial is preferred over a Poisson regression because of the potential overdispersion. Fall rates for participants with follow-up times of less than 6 months will be adjusted by accounting for their exposure time. The model will include intervention type, trial site, BBS score and age as the independent variables. The incidence rate ratios between interventions will be calculated from the model with a two-sided 95% CI. To consider the potentially present excess of zeroes, a zero-inflated negative binomial model will be used as a sensitivity analysis. Other secondary endpoints will be analysed with the appropriate regression models.

Safety analyses will be performed for all participants for whom one of the interventions is started, and participants will be analysed according to the intervention received. The rates of adverse events and serious adverse events will be calculated with a two-sided 95% CI. No formal interim analyses of the efficacy endpoints will be performed.

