#### How

EYT and Tai Chi will be provided in one-hour sessions, in groups of 4–6 participants, and may include a resting time (approximately 15 min) in the end. For practicing at home, participants receive oral, written (manual) and audio-visual instructions.

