The strengths of the ENTAiER trial lie in the highly relevant issues of aging population, increasing burden of mostly lifestyle-related multimorbidity and high risk of falls increasing morbidity, mortality and costs; the methodological rigor, the multi-disciplinary team and its high competence and experience; and the data quality and conformity to the ICH-GCP. Moreover, the active and constant involvement of the PPR improved the trial quality and its consequent adjustment to patients’ needs, values, goals and capabilities. Transparency is highly valued in this study. Aside from the PPR, the design has been discussed with many experts in the field, organisations representing or supporting senior citizens and healthcare providers. The treatment manuals and videos will be published after the termination of the trial to enable replicability or to implement them in future care. They further enable the autonomy of participants for independent practicing beyond group classes. We attempt to enrol older people who lead a reclusive life, are economically disadvantaged and have an increased risk of falling [51] but seldom visit exercise classes or other activities of their own accord. The participation of these people is supported by a specific motivational concept and by an appreciating and non-judgmental communication through the study personnel, teachers and therapists.

The ENTAiER trial has some limitations. First, the focus of the trial tends towards a pragmatic assessment at the expense of explanatory interpretation. Therefore, the result will assess the combination of exercises and teachers’/therapists’ ability to instruct, motivate and individually tailor exercises. The differences between therapists cannot be captured. However, more than 20 therapists and 20 teachers in different settings (trial sites, places for group settings and groups) will provide EYT and Tai Chi, levelling out the effects of specific personalities and settings. We will also monitor the adherence to home and group training, the adherence to and adaption of exercises by the therapists and teachers, the participants’ subjective impression of what motivated them and the inner coherence with practices.

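### The fall models leave out class and instructor clustering in the two exercise arms; if such clustering exists, the nominal 5% closed test exceeds 5%, slightly or materially depending on an ICC that the protocol does not give

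*Protocol article*

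**What the plan says.** In the Protocol article, Interventions (How), both active treatments are given "in groups of 4–6 participants". Under Randomisation, each site allocates in blocks of 12, 15 or 18 at 1:1:1. That puts 12/3 = 4, 15/3 = 5 or 18/3 = 6 people in each arm, which matches the class size, so a block yields about one EYT class and one Tai Chi class. Standard care is a brochure and a recommended visit to the primary care doctor, with no classes.

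Under Statistical analysis, the primary Cox model is described thus: "The model will include the intervention type, trial site, BBS score and age as the independent variables". For the negative binomial model of the number of falls: "The model will include intervention type, trial site, BBS score and age as the independent variables". Neither description mentions class, instructor, a frailty term or a clustered variance. On error control, "a closed test procedure at the two-sided level alpha of 5% will be used": a global three-group test, then pairwise tests. The section on blinding says that the confirmatory analyses are all laid down in advance in the trial protocol.

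The Discussion accepts that the result reflects the instructor's ability as well as the exercises, and that therapist differences cannot be separated out. Its answer is that more than 20 therapists and 20 teachers take part, "levelling out the effects of specific personalities and settings".

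**The concern.** This is a partially nested trial: outcomes may be correlated within classes or instructors in two arms and not in the third. People taught together by one instructor may fall more alike than people taught apart, and the Discussion names the route itself.

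The number of instructors does not settle the matter. Many instructors make the average effect representative, but the variance between them remains part of the sampling error, and a model that assumes independent participants leaves it out. The site term does not replace it, because classes and instructors vary within site and arm. The negative binomial dispersion parameter covers variation between persons, not correlation between classmates.

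At stake are the level of the closed test, which is the only stated protection against multiplicity, and the width of the hazard-ratio and rate-ratio intervals.

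**Working it through.** **The plan's own figure.** The sample size section states: "The sample size calculation is performed for the three-group comparison". The faller proportion "is 50% with standard care and 35% with both EYT and Tai Chi", and "The study is planned with 80% power to show the difference between treatments". The mean proportion is (0.50 + 0.35 + 0.35)/3 = 0.40, and the squared deviations sum to 0.01 + 0.0025 + 0.0025 = 0.015. The noncentrality per participant per arm is 0.015/(0.40 × 0.60) = 0.0625. At n = 155 it is 9.69, and the 2-df chi-square test has power 80.2% (79.96% at n = 154). The stated 155 per group reproduces, with no design effect in it.

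**Inputs for clustering.** Class size m = 4 to 6 (from How). ICC = 0.01 to 0.10 is an assumption. Design effect DE = 1 + (m − 1) × ICC in EYT and Tai Chi, and 1 in standard care.

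**Formulas.**
- True SE / model SE, active versus standard care: √((1 + DE)/2).
- True SE / model SE, EYT versus Tai Chi: √DE.
- Pairwise size: 2 × [1 − Φ(1.96 / SE ratio)].
- Global size: under no average difference, the model's 2-df statistic behaves as DE·χ²₁ + ((2 + DE)/3)·χ²₁, with independent terms, and is compared with 5.991.

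**Example (m = 5, ICC 0.05).** DE = 1.20. The SE ratios are √1.10 = 1.049 and √1.20 = 1.095. The sizes are 6.2% (active versus standard care), 7.4% (EYT versus Tai Chi) and 7.1% (global).

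**Range over m = 4 to 6.**

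| Assumed ICC | Global test | Active vs standard care | EYT vs Tai Chi |
|---|---|---|---|
| 0 | 5.0% | 5.0% | 5.0% |
| 0.01 | 5.3–5.5% | 5.2–5.3% | 5.4–5.6% |
| 0.02 | 5.6–6.0% | 5.4–5.6% | 5.7–6.2% |
| 0.05 | 6.6–7.7% | 5.9–6.5% | 6.8–8.0% |
| 0.10 | 8.3–10.6% | 6.8–8.0% | 8.6–11.0% |

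**Check on time-to-event data.** The three-arm closed log-rank test (score form of the Cox test, no covariates) was simulated with a class-level log-normal frailty in the active arms, 180 per arm and 20,000 runs per setting. For m = 4 to 6 its size was 4.9–5.0% at ICC 0, 5.3–5.5% at 0.011, 5.7–6.2% at 0.021, 6.6–7.6% at 0.049 and 8.5–10.6% at 0.096. The approximation carries over. The negative binomial model was not simulated.

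**Price of modelling it.** The noncentrality becomes n × 0.0625 × 3/(2 + DE), so n per arm is about 155 × (2 + DE)/3. Over m = 4 to 6, 80% power needs 156–157 per arm at ICC 0.01, 158–160 at 0.02, 162–168 at 0.05 and 170–180 at 0.10. About 550/3 = 183 per arm are to be randomised.

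**The case against.** The strongest objection is that the text lists covariates and not a variance estimator. A robust variance would contradict nothing in it and could stand in an analysis plan or in the full protocol, neither of which is shown. This stands in part, so the omission cannot be read as a refusal to allow for clustering. But the article specifies its confirmatory model in detail, says such analyses are fixed in advance, and takes up instructor differences directly, with averaging as the only remedy. That reasoning is incomplete as stated.

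Three further points stand and limit the claim:
- **No ICC is given.** Some features may keep it low: manuals, individual tailoring, and home practice on non-class days. At 0.01–0.02 the excess is under about one percentage point for the global test.
- **If classes affect no one, they add no correlation and the level holds.** Inflation of the global test needs real class-to-class variation around a zero average effect. This reservation is weaker for EYT versus Tai Chi, where both treatments may work equally well on average and still vary between classes, and it does not rescue interval coverage.
- **Only variation specific to an arm counts.** Correlation shared by all arms at a site or in a batch is handled by the site term and by randomisation within batches.

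A reader might infer that the standard errors are too small and the test above 5% as established fact. The documents do not support that without a positive ICC. A reader might also take about 14% as the likely size, from clustering by instructor with about 183/20 ≈ 9 participants each and ICC 0.10 (DE = 1.8). That stacks the highest ICC on an upper-end caseload (the article says more than 20 therapists) and assumes that people in different classes of one instructor are as alike as classmates.

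**Conclusion.** The point holds as a conditional one. As described, both fall models take participants as independent within site, although two of the three arms are taught in small classes by shared instructors, and the Discussion's answer addresses the average effect and not its standard error. For any positive arm-specific ICC, the error is in the anti-conservative direction. For classes of 4 to 6 the consequence is minor at ICC 0.01–0.02 and material near 0.05–0.10, with EYT versus Tai Chi affected most. The ICC range is an assumption, and the tabulated figures take the class as the cluster. The negative binomial model shares the omission, but its size is not quantified. This warrants a change before analysis; it is not a demonstrated failure of error control.

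**What to change.** Keep both models and all covariates. Prespecify, for the global and pairwise Cox tests and for the negative binomial model:
- A cluster-robust variance with a named small-sample correction, since there are only some 20 instructors per active arm. A shared frailty in the active arms is an acceptable alternative; choose one in advance.
- One cluster unit, named in advance. The instructor is a sensible choice because it contains the classes.
- Cluster membership by the class or instructor allocated at randomisation, whether or not the person attends, so that the intention-to-treat set is fully assigned.
- Each standard-care participant as a cluster of one.

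Record the class and instructor identifier in the analysis data set. Instructors keep attendance lists, but the article does not say that this identifier reaches the electronic case report form. In the Discussion, replace the averaging argument with a statement of this method.

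The cost is slightly wider intervals and a little power. With class clustering over the assumed range, power of the global test at 155 per arm falls from 80.2% to between 79.8% (ICC 0.01, m = 4) and 73.5% (ICC 0.10, m = 6). At 183 per arm without loss it stays between 80.7% and 86.3%. The 183 also has to cover losses: 3 × 155 = 465 of 550 leaves about 15.5%. With the instructor as unit, 9 participants each and ICC 0.10, the formula above gives 155 × 3.8/3 ≈ 196 per arm, more than planned; at ICC 0.05 it gives 155 × 3.4/3 ≈ 176, which is within the number randomised.
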